### Location of the study and event

The 2,200 participants of the experimental group will be randomly assigned to one of the two indoor venues called “La Machine du Moulin Rouge” or “La Bellevilloise.” The reservation group of participants will be assigned to the same venue to respect the randomization by block.

“Machine du Moulin Rouge” is a venue with a surface area of 500 m^2^. It has two bars and two ventilation systems: one at the central bar whose ventilation capacity is 10,627 m^3^/h, and another on the main stage whose capacity is 11,000 m^3^/h (Figure 1). “Bellevilloise” is a venue with a surface area of 450 m^2^ and has only one bar. Its ventilation system operates at 7,500 m^3^/h thanks to two machines located at the dance floor and bar levels (Figure 2).

**Figure 1 F1:**
[figure not shown]
Plan of the room “La Machine du moulin rouge” and location of the AerosolSense™ and ventilation.

**Figure 2 F2:**
[figure not shown]
Plan of the room “La Bellevilloise” and locations of the AerosolSense™ and ventilation.

The doors will be open from 11 to 6 pm and participants can arrive at any time. The music program will be composed of eight disk jockeys (DJs) distributed over the two venues. The timetable and distribution of DJs in each venue will not be known to the participants to avoid selection bias. The ventilation systems will be started 3 h before the event. During the experiment, masks are not mandatory except for staff and no social distancing measures will be required. The hydro-alcoholic gel will be made available at various locations.

Three AerosolSense™ systems (Thermo Fisher) at “Machine du Moulin Rouge” and one at “Bellevilloise” will be installed to detect viruses in the air. The system will be used to determine viral contamination in the 12 h prior to the start of the event, during the entire event (11 pm−6 am), and for 12 h after the event.

The cartridges of each instrument used for each period will be tested using a multiplex PCR detecting a panel of respiratory viruses, including SARS-CoV-2 (Filmarray Respiratory Panel 2.1, bioMérieux^®^). For SARS-CoV-2 positive samples, semi-quantitative estimations will be performed using real-time RT-PCR technique with the determination of the cycle threshold (Ct).

### Primary endpoint

The primary endpoint is the number of participants in each group with a positive salivary SARS-CoV-2 RT-PCR on day 7 after the date of the event.

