**Methods and analysis:**

Four thousand four hundred healthy volunteers aged 18–49 years and fully vaccinated will be included in Paris region. The intervention is an 8-hour indoor clubbing event with no masks, no social distance, maximum room capacity, and ventilation. A reservation group of up to 10 people will recruit participants, who will be randomized 1:1 to either the experimental group (2,200 volunteers in two venues with capacities of 1,000 people each) or the control group (2,200 volunteers asked not to go to the club). All participants will provide a salivary sample on the day of the experiment and 7 days later. They also will answer several questionnaires. Virological analyses include polymerase chain reaction (PCR) of salivary samples and air of the venue, investigating SARS-CoV-2 and 18 respiratory viruses.

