#### Objective

The primary objective is to assess the absence of an increase in the risk of SARS-CoV-2 infection 7 days after an indoor club event in the group participating in the event, being fully vaccinated and without a face mask, compared to a non-participating group.

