### Secondary endpoints

Secondary endpoints are:

Numbers of asymptomatic, symptomatic, and severe SARS-CoV-2 infections according to a self-assessment by a questionnaire sent online from D3 to D10 after the date of the event, and medical follow-up.Whole-genome sequencing of SARS-CoV-2 detected in participants' samples.Comparison of the sequences of the complete SARS-CoV-2 genomes in the participants with a positive test on D7.Detection of seasonal respiratory viruses including SARS-CoV-2 in the air, by the AerosolSense™ system (Thermo Fisher Scientific).Assessment of acceptability to download and use the recommended tracking application (“TOUSANTICOVID”) through surveys sent online after the party (eCRF) (27).Adherence to the health protocol by a questionnaire sent online to participants and organizers after the evenings.Online questionnaire on motivation and barriers to COVID-19 vaccine and *COVID Certificate* (Digital or paper presentation of health proof, according to the regulations in force).Survey of close contact behavior during the event.Number of participants in each group with a positive seasonal respiratory viruses PCR on day 7 after the date of the event.Numbers of asymptomatic, symptomatic, and severe seasonal respiratory virus infections according to a self-assessment by a questionnaire sent online from D3 to D10 after the date of the event, and medical follow-up.Detection of seasonal respiratory viruses in the participant's saliva at D0/D7 by RespiFinder^®^ 2Smart assay (PathoFinder).

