#### Analysis of the primary endpoint

The primary endpoint of the current study is positive SARS-CoV-2 proportion in saliva samples 7 days after the event in the experimental group compared to the non-experimental groups. Statistical analyses were performed on an intention-to-treat basis.

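### The primary endpoint counts every day-7 positive, including people already PCR-positive on day 0, which pulls the relative risk towards 1 and favours non-inferiority

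*Protocol article*

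**What the plan says.** The Primary endpoint section of the protocol article reads: "The primary endpoint is the number of participants in each group with a positive salivary SARS-CoV-2 RT-PCR on day 7". Analysis of the primary endpoint compares the arms on the "positive SARS-CoV-2 proportion in saliva samples 7 days after the event" and adds: "Statistical analyses were performed on an intention-to-treat basis". Neither section mentions the day-0 result.

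The day-0 result will exist. The abstract says: "All participants will provide a salivary sample on the day of the experiment and 7 days later". Participant timeline and the follow-up table confirm a day-0 saliva PCR in both arms. Experimental participants bring the sample to the venue; control participants post it.

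The stated objective is to "assess the absence of an increase in the risk of SARS-CoV-2 infection 7 days after an indoor club event". Sample size computation sets the margin at five times the control incidence and builds the sample size from weekly incidence. Non-inclusion criteria remove only people with COVID-19 symptoms or a confirmed diagnosis in the two weeks before the event. Strengths and limitations presents entry without a test as a novel feature of the trial.

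A secondary endpoint uses the same kind of count for other viruses: "Number of participants in each group with a positive seasonal respiratory viruses PCR on day 7". A separate secondary endpoint lists detection of these viruses in saliva at both day 0 and day 7.

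**The concern.** A person who is PCR-positive before going in was not infected at the event. Undiagnosed carriers without symptoms are eligible, are randomised and may attend, and any who still shed on day 7 count as primary events. Randomisation spreads them equally over the arms in expectation. Adding the same number of old infections to both arms moves a ratio above 1 towards 1.

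In a superiority trial that would be conservative. Here the margin is a multiple of the control rate, so carry-over shrinks the observed ratio and also enlarges the absolute excess that the margin permits. Both effects favour the conclusion that the trial hopes to reach. For the seasonal viruses, where the Hypothesis section expects an increase, the same dilution would hide it.

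**Working it through.** **1. The plan's own figures.** The stated detectable relative risks are 4.4 and 3 with 2,000 per arm, 80% power and 5% alpha, at 100 and 300 positive tests per 100,000 per week.

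- Control risk = weekly incidence / 0.38 × 0.2 (reading the under-detection figure as 38% detected, with an 80% vaccine effect). This gives 0.0526% and 0.158%.
- Detectable RR = 1 + (1.645 + 0.842) × √(2p(1 − p)/2,000) / p, one-sided 5%.
- Results: 4.43 and 2.98, which match the stated 4.4 and 3.

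The inputs are weekly new infections: 2,000 × 0.0526% = 1.05 and 2,000 × 0.158% = 3.16 expected control events. The sample size therefore counts new infections, while the endpoint counts new plus old.

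**2. Dilution.** Let c be the share of control day-7 positives already positive on day 0, and RR the true ratio among day-0 negatives.

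- Observed RR = c + (1 − c) × RR.
- With RR = 5 this is 5 − 4c: 4.2 at c = 0.20, 3.7 at 0.33, 3.0 at 0.50 and 2.3 at 0.67.

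A risk-difference analysis does not escape this. With new-infection risk p in the control arm and RR = 5, the true excess is 4p. The margin permits an excess of four times the observed control rate, which is 4p/(1 − c), or 8p at c = 0.5.

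**3. A range for c.** The documents give no value. Assume steady incidence and PCR positivity lasting d days, with d from 10 to 21. Of the people positive on day 7, a share (d − 7)/d was already positive on day 0.

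| | d = 10 | d = 21 |
|---|---|---|
| c, no effect of exclusions | 3/10 = 0.30 | 14/21 = 0.67 |
| Observed RR if true RR is 5 | 3.8 | 2.3 |
| c, exclusions remove half of prevalent cases | 1.5/8.5 = 0.18 | 7/14 = 0.50 |
| Observed RR if true RR is 5 | 4.3 | 3.0 |

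**4. False non-inferiority.** Setting: 2,000 per arm, one-sided 5% conditional exact test of RR ≥ 5, true RR of 5 among day-0 negatives.

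| c | Control incidence 0.158% | Control incidence 0.0526% |
|---|---|---|
| 0 | 2.8% | 2.2% |
| 0.20 | 6.0% | 3.7% |
| 0.33 | about 10% | 5.4% |
| 0.50 | about 22% | about 10% |
| 0.67 | about 51% | about 21% |

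**5. The price of removing carry-over.** At a true RR of 1, control incidence 0.158% and c = 0.5, the same test shows non-inferiority with probability 75% if carry-over is counted and about 46% if it is removed.

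**The case against.** **The article is condensed.** The full protocol or an analysis plan may say how day-0 positives are handled, and the sample-size text does speak of incidence. Nothing shown supports the inference that the sponsor will ignore the day-0 results. But the article states the endpoint, and states its analysis separately, without that condition. A reader who follows it would count carry-over, so this is a stated rule that needs correcting and not a detail left out.

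**The size is uncertain.** This stands. The value of c is an assumption, and at the lower incidence with c up to about 0.33 the false-declaration rate stays near or below the nominal 5%. A reader might infer that any observed RR below 5 means non-inferiority will be declared. It does not: the confidence limit must lie below the margin, which is why the table in step 4 is the relevant measure.

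**A larger dilution is tempting.** One could treat everyone infected before the event as old, including those infected two or three days earlier, and get an observed RR of 1.8 to 3.0. That overstates what a day-0 rule can correct. People infected just before the event test negative on day 0 and stay in the corrected endpoint. With a two- to three-day lag to positivity, a five-fold rise in post-event infection would still show as 1 + 4 × 5/7 = 3.9 to 1 + 4 × 4/7 = 3.3 after the correction.

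**Conditioning on day 0 brings its own risk.** The ticket is emailed the day before the event, so the day-0 sample can follow knowledge of the arm, and its collection differs by arm. If posted control samples go missing more often, more carry-over stays in the control arm and the ratio is again lowered. This stands as a reason for reporting and a sensitivity analysis. It does not justify counting all carry-over.

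**Seasonal viruses.** The day-7 count has the same weakness, but it is secondary, has no stated margin, and day-0 detection is already listed. It would be wrong to say that baseline status is unavailable there.

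**Conclusion.** The point holds. The endpoint as stated does not match the objective, the margin or the sample size, and the mismatch favours non-inferiority. The direction is certain for any true RR above 1, provided some day-0 positives are still positive on day 7. The size rests on c, and so on the assumed duration of positivity, steady incidence and the effect of the exclusions. It ranges from little change in error rate (c about 0.2, lower incidence) to a false-declaration rate of about one in two (c = 0.67, higher incidence). The trial's primary conclusion could be reached because of infections that the event did not cause, so this should be corrected before the primary analysis.

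**What to change.** - Define the primary endpoint as a positive day-7 saliva PCR among participants not positive on the day-0 sample.
- Report missing day-0 samples by arm, and add a sensitivity analysis restricted to documented day-0 negatives.
- Report all day-7 positives as a secondary result.
- Apply the same rule virus by virus to the seasonal-virus day-7 count, using the day-0 results already planned.

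No new samples are needed. The cost is not negligible: at c = 0.5 half of the control events leave the count, with the loss of power shown in step 5 of the working. That power came from infections the event could not have caused. Infections acquired just before day 0 and not yet detectable remain in the endpoint, and the report should say so.

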### Secondary endpoints

Secondary endpoints are:

Numbers of asymptomatic, symptomatic, and severe SARS-CoV-2 infections according to a self-assessment by a questionnaire sent online from D3 to D10 after the date of the event, and medical follow-up.Whole-genome sequencing of SARS-CoV-2 detected in participants' samples.Comparison of the sequences of the complete SARS-CoV-2 genomes in the participants with a positive test on D7.Detection of seasonal respiratory viruses including SARS-CoV-2 in the air, by the AerosolSense™ system (Thermo Fisher Scientific).Assessment of acceptability to download and use the recommended tracking application (“TOUSANTICOVID”) through surveys sent online after the party (eCRF) (27).Adherence to the health protocol by a questionnaire sent online to participants and organizers after the evenings.Online questionnaire on motivation and barriers to COVID-19 vaccine and *COVID Certificate* (Digital or paper presentation of health proof, according to the regulations in force).Survey of close contact behavior during the event.Number of participants in each group with a positive seasonal respiratory viruses PCR on day 7 after the date of the event.Numbers of asymptomatic, symptomatic, and severe seasonal respiratory virus infections according to a self-assessment by a questionnaire sent online from D3 to D10 after the date of the event, and medical follow-up.Detection of seasonal respiratory viruses in the participant's saliva at D0/D7 by RespiFinder^®^ 2Smart assay (PathoFinder).

### Data collection

The trial will be conducted in accordance with relevant regulations and standard operating procedures, including data protection. The data will be collected on an electronic case report form. All necessary precautions to ensure the confidentiality of information regarding investigational medicinal products, trial participants, and in particular the identity of the participants and the results obtained will be taken.

### Statistical considerations

#### Sample size computation

In a non-inferiority design, the sample size depends on the probability of the observed event (here a SARS-CoV-2 infection), the power of the study, and a threshold of clinical significance.

To define this threshold, we consider that the exposure of a vaccinated population to the event has to lead to an equal or less number of secondary infections than in a non-exposed unvaccinated population. However, according to the risk/benefit balance and the random assignment, both our control and intervention arms need to be fully vaccinated. Consequently, we need to estimate the level of infection which could have been observed in the control group if it had not been vaccinated. Assuming a vaccine efficacy against infection of 80% would mean that the risk of infection is divided by 5, hence we consider that the incidence observed in the control group could have been multiplied by 5 if the control group was not vaccinated. Consequently, we set the non-inferiority threshold to five times the incidence observed in the control group.

As shown in Figure 3, the additional risk could be detected as a function of incidence and sample size, with 80% power and alpha risk of 5%. We corrected observed incidence rates in the population to account for 38% under-detection and 80% vaccine protective effect, as observed in France in 2020 (28).

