### The vaccine against COVID-19 and its efficacy on the delta variant and its transmission

The approved COVID-19 vaccines have lower effectiveness against mild forms of SARS-CoV-2 infections but remain effective to prevent hospitalizations (13–15). Contrasting results have been published regarding the transmission of SARS-CoV-2 among vaccinated. Evidence of the COVID-19 outbreak in a large, vaccinated population have been reported in Provincetown (USA) (16), which has also shown a superspreading event, while transmission in a healthcare setting occurred in Vietnam (17). However, another study in the USA showed few work-related secondary cases in vaccinated healthcare workers. A recent prospective cohort study in the UK found a modest protective effect on COVID-19 transmission (18): The secondary attack rate (SAR) in household contacts exposed to the delta variant was 25 and 38% in vaccinated and unvaccinated contacts, respectively. SAR among household contacts exposed to fully vaccinated index cases (25%; 95% CI 15–35) was similar to household contacts exposed to unvaccinated index cases (23%; 15–31).

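### The five-fold margin rests only on an assumed 80% vaccine efficacy that the protocol does not support for Delta, and meeting it excludes a five-fold increase rather than showing no increase

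*Protocol article*

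**What the plan says.** **Margin.** In the protocol article, *Sample size computation*, the guiding principle is that exposing vaccinated people to the event "has to lead to an equal or less number of secondary infections than in a non-exposed unvaccinated population". Both arms are vaccinated, so the unvaccinated risk has to be inferred. The inference is one step: "Assuming a vaccine efficacy against infection of 80% would mean that the risk of infection is divided by 5", and so "we set the non-inferiority threshold to five times the incidence observed in the control group". No other argument for the value 5 is given. The next paragraph corrects population incidence "to account for 38% under-detection and 80% vaccine protective effect, as observed in France in 2020".

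**Delta.** The *Discussion* and *Strengths and limitations* place the trial in Delta circulation. The introductory section on vaccine efficacy against Delta says "The approved COVID-19 vaccines have lower effectiveness against mild forms of SARS-CoV-2 infections" and reports household secondary attack rates of 25% in vaccinated and 38% in unvaccinated contacts. *Rationale, knowledge gap, and issues* uses reduced protection against transmission as a reason for the trial.

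**Claim.** *Objective* sets out to "assess the absence of an increase in the risk of SARS-CoV-2 infection 7 days after an indoor club event", compared with the non-participating group, which is also vaccinated. *Hypothesis* likewise states that attendance carries no increased risk.

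**The concern.** Two separate links need to hold.

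First, the margin equals the ratio of unvaccinated to vaccinated risk, so it is only as good as the efficacy put into it. The article uses reduced protection under Delta to justify the study, then assumes high protection to set the margin. If efficacy is below 80%, a margin of 5 lies above the very risk it was meant to cap.

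Second, the margin and the objective answer different questions. The margin asks whether attendees do worse than hypothetical unvaccinated people who stayed away. The objective asks whether they do worse than the vaccinated controls. A trial that meets the margin could be reported as showing no increased risk while its data still allow an increase of several fold, on a question that bears on opening nightclubs.

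**Working it through.** **Inputs** (*Sample size computation* unless noted): 2,000 analysed per arm; 80% power; alpha 5%, sidedness not stated; incidence 100 to 300 per 100,000 per week; corrections of 38% and 80%; margin RR 5; stated detectable RR 4.4 and 3. Delta attack rates of 25% and 38% come from the introduction.

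**1. The plan's own figures.** The formula is not printed. The stated figures are reproduced by a difference-scale calculation with unpooled variance, true RR 1, one-sided 5%, and 38% read as the share of infections detected (although the text calls it under-detection):

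- p0 = incidence / 0.38 × 0.20 = 52.6 and 157.9 per 100,000, or about 1.05 and 3.16 control events in 2,000.
- Detectable RR = 1 + (1.645 + 0.842) × √[2·p0(1 − p0)/2,000] / p0 = 4.43 and 2.98, against the stated 4.4 and 3.

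One-sided 2.5% gives 4.86 and 3.23, which does not match.

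**2. Margin by efficacy.** Margin = 1/(1 − VE), with VE the vaccine efficacy. At 80%, 1/0.20 = 5. From the household figures, VE = 1 − 25/38 = 34% and the margin is 38/25 = 1.52.

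| VE | Margin |
|---|---|
| 80% | 5.0 |
| 70% | 3.3 |
| 60% | 2.5 |
| 50% | 2.0 |
| 34% | 1.5 |

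The smaller margins are out of reach at this size. With p0 recalculated at 34% efficacy, the formula in step 1 gives a detectable RR of 2.9 to 2.1, and a margin of 1.52 would need 26,368 to 8,759 per arm (incidence 100 to 300).

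**3. What can pass a margin of 5.** Two tests are shown because the article names none. With a fixed absolute margin of 4·p0, as in step 1, the probability of passing is Φ{(5p0 − p1)/√[(p0(1 − p0) + p1(1 − p1))/2,000] − 1.645}, where p1 = RR·p0. For incidence 100 and RR 3: 0.001053/0.001025 − 1.645 = −0.618, so Φ = 26.8%. The exact ratio test treats attendee events, given the total, as binomial with probability 5/6 at the margin (one-sided 5%); its figures are simulated.

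| True RR | Fixed margin, incidence 100 | Fixed margin, incidence 300 | Exact ratio, incidence 100 | Exact ratio, incidence 300 |
|---|---|---|---|---|
| 1 | 89.6% | >99% | 15.1% | 46.6% |
| 2 | 55.3% | 92.5% | 8.9% | 25.5% |
| 3 | 26.8% | 55.4% | 5.5% | 12.5% |
| 5 | 5.0% | 5.0% | 2.2% | 2.9% |

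**The case against.** **The household figures are not efficacy against infection.** They are conditional on living with a case, come from one cohort that the article introduces as part of a mixed literature, and carry no interval for the 38%. The general statement on Delta gives no number, and since the article quotes more than 90% for pre-alpha and alpha, 80% is already lower. This stands. A reader might infer that the correct margin is 1.5; the documents do not show that. They show that 80% has no Delta support in the article and that its one quantified comparison points well below it.

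**The date of the 80%.** A reader might infer from "80% vaccine protective effect, as observed in France in 2020" that the efficacy behind the margin is a 2020 figure. In the full phrase the date may belong to the under-detection alone, and the sentence that sets the margin gives neither date nor source. The point does not need that reading. Nor does the article anywhere describe 80% as protection against Delta; it names no variant.

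**A three-fold increase does not simply satisfy the criterion.** A true RR of 3 lies inside the margin, but the upper confidence limit must also fall below 5. With 9 versus 3 events, a Wald limit on the log scale is 3 × exp(1.645 × √(1/9 + 1/3)) ≈ 9, which fails. This also stands, and it is why step 3 gives probabilities. The low pass rates of the ratio test go with low power even when attendance has no effect (15–47%).

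**The design is disclosed.** The article says the trial is non-inferiority, states the margin and its comparator, and the abstract words the primary objective as determining the relative risk. That helps a careful reader, but it does not bring the *Hypothesis* and *Objective* wording into line with a margin that tolerates a 400% relative increase.

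**Conclusion.** The concern holds on both counts, within limits. The margin of 5 depends entirely on an assumed 80% efficacy that the article does not support for the period it studies. For any efficacy below 80%, the margin exceeds the unvaccinated, unexposed risk it was meant to cap: 3.3 at 70%, 2.0 at 50%, 1.5 at 34%. The range is shown because the documents do not fix the Delta value.

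Independently of that, meeting the margin excludes an RR of 5 or more and nothing stronger. A true doubling would pass 55–92% of the time and a tripling 27–55% under the fixed absolute margin, or about 9–25% and 6–13% under an exact ratio test. These figures assume 2,000 analysed per arm, one-sided 5%, and control risks built with 38% as the detected share and 80% efficacy. The sample-size arithmetic itself reproduces and is not at fault.

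**What to change.** 1. Reword the hypothesis, the primary objective and the permitted conclusion to excluding a five-fold or greater increase in risk against vaccinated non-participants.
2. State that 80% efficacy is an assumption not specific to Delta, and tabulate the margin 1/(1 − VE) over 34–80%.
3. Report the RR with its upper confidence limit against that table. Claim that risk is not above that of unexposed unvaccinated people only conditionally, naming the efficacy assumed.

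The cost is wording and one table. Neither the sample size nor the conduct changes, so this can be done although recruitment has begun. The price is a weaker claim: at 2,000 per arm the conditional statement would rarely be attainable for the lower efficacies. At a margin of 1.52 power is 17–32% with control risk recalculated at 34% efficacy, and 10–16% with it kept at the planned level.

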**Figure 3 F3:**
[figure not shown]
Minimal detectable relative risk depending on the number of subjects in the intervention group for different levels of incidence of SARS-CoV-2 infection detected in the general population. With 2,000 subjects in each arm (intervention and control), we have a power of 80% to detect a relative risk of 3–4.4 depending on the level of SARS-CoV-2 incidence.

For incidences in the general population of between 100 and 300 positive tests per week per 100,000 people, the detectable excess risk would be between 4.4 and 3 (respectively) for 2,000 participants in the intervention group and 2,000 participants in the control group (ratio 1:1; Figure 3). We simulated the impact of the clustering effect, considering an increased risk of infection within groups of participants who came together to the event. Considering that the secondary attack rate within those groups would be decreased by 80% by the vaccine protection, we could assume that the intra-cluster correlation would be negligible and that the design effect would be close to 1. With a planned attrition rate of 10% of participants for the primary outcome on D7, we plan to randomize a total of 2,200 participants in the “experimental” arm and 2,200 in the “control” arm.

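### The five-fold margin is tied to the observed control incidence and planned as if known: plugged in that way, type I error is about 23%; tested as a fixed RR of 5, the 80% power does not apply

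*Protocol article*

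**What the plan says.** The protocol article, under Sample size computation, derives the factor of five from an assumed vaccine efficacy: "Assuming a vaccine efficacy against infection of 80% would mean that the risk of infection is divided by 5". It then sets the margin: "Consequently, we set the non-inferiority threshold to five times the incidence observed in the control group". No absolute value for the margin is given.

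The same section adjusts the planning incidence: "We corrected observed incidence rates in the population to account for 38% under-detection and 80% vaccine protective effect". With alpha 5% (sidedness not stated) and 80% power, the text below Figure 3 says that "the detectable excess risk would be between 4.4 and 3 (respectively) for 2,000 participants in the intervention group and 2,000 participants in the control group", for general-population incidences from 100 to 300 per 100,000 per week. The Figure 3 caption gives the same result as a relative risk: "we have a power of 80% to detect a relative risk of 3–4.4 depending on the level of SARS-CoV-2 incidence".

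The section on analysis of the primary endpoint compares day-7 positive proportions by intention to treat. It names no test, interval or effect scale. The abstract states the primary objective as a relative risk.

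**The concern.** Five times an observed proportion is an estimate, and it carries the control arm's sampling error multiplied by five. With one to three control positives expected, that error is large. A test that treats the threshold as a known number leaves this error out and passes too easily.

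The error in question is the one that matters most here: concluding that indoor clubbing does not materially raise infection when it raises it five-fold. A test that does carry the error is valid but needs more information than the sample-size calculation allowed for. Either the type I error or the stated power is therefore affected, depending on how the margin sentence is read.

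**Working it through.** **Inputs.** From the article: 2,000 per arm evaluable, alpha 5%, power 80%, incidence 100 and 300 per 100,000, vaccine effect 80%, correction factor 38%, margin factor 5. Assumed: alpha is one-sided, and 38% is the share of infections detected (divide by 0.38). The text speaks of 38% under-detection, which would more naturally mean dividing by 0.62. Clustering is ignored, in line with the article's design effect close to 1.

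**1. Reproducing the stated figures.** Control risk p = incidence / 0.38 × 0.2:
- 100 per 100,000: p = 0.0526%, or 1.05 expected control positives in 2,000.
- 300 per 100,000: p = 0.158%, or 3.16 expected.

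The risk-difference formula with known margin (RR − 1)p and true RR = 1 is n = (1.645 + 0.842)² × 2p(1 − p) / [(RR − 1)p]².
- RR 4.4 at p = 0.0526%: n = 2,032.
- RR 3 at p = 0.158%: n = 1,955.
- Solved for RR at n = 2,000: 4.43 and 2.98, against 4.4 and 3 stated.

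Other variants tried do not reproduce the figures: one-sided 2.5% gives n = 2,579 and 2,482, division by 0.62 gives 3,315 and 3,192, and log-RR and pooled superiority formulas also fail. At the adopted five-fold margin (difference 4p, still taken as known) the same formula gives power of 89.6% and 99.96% with 2,000 per arm.

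**2. Type I error if the observed margin is plugged in as a constant.** Let E and C be the positives in the club and control arms. The rule is: upper one-sided 95% bound of the risk difference below 4 × the observed control risk. For rare events this is E + 1.645√(E + C) < 5C. At a true RR of 5 with λ expected control positives, the rule uses variance 5λ + λ = 6λ. The true variance of E − 5C is 5λ + 25λ = 30λ.
- Large-sample value: Φ(−1.645 × √(6/30)) = Φ(−0.736) = 23.1%.
- Exact enumeration of two binomials: 23.6% at 100 and 23.3% at 300 per 100,000.
- Bounding the club risk alone against 5 × the observed control risk: 17–25%, depending on the interval.
- One-sided 2.5%: 17.3% and 20.0% exact.

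**3. A fixed RR of 5 tested with both arms' error, one-sided 5%.**

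| Method | Type I error at RR = 5 (100; 300 per 100,000) | Power at RR = 1 (100; 300 per 100,000) |
|---|---|---|
| Conditional exact | 2.2%; 2.8% | 15%; 46% |
| Mid-P | 3.9%; 4.5% | 23%; 55% |
| Log-RR Wald | 5.1%; 5.8% | 13%; 56% |
| Score | 6.8%; 6.1% | 39%; 65% |

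**4. Example with 3 control positives.** Nine club positives pass the plug-in rule: 9 + 1.645√12 = 14.7 < 15. Against RR = 5 the exact p-value is 0.32, mid-P 0.22 and the score z −0.78, so all three fail. The largest passing club count is 2 (exact), 3 (mid-P) or 4 (score).

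**5. Zero control positives.** The probability is (1 − p)^2000. It is 35% and 4% at 100 and 300 per 100,000 with division by 0.38, or 52% and 14% with division by 0.62.

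**The case against.** The strongest reply is that type I error belongs to a test and the article names none. The factor of five is derived before any data, and a threshold of five times the control incidence is algebraically RR < 5. The abstract and Figure 3 speak of relative risk. On that reading the margin is a constant and type I error is near nominal. A planning formula that inserts an assumed control risk is standard and does not prove that the analysis will do the same. The choice of interval and the handling of sparse cells can properly sit in the full protocol or the SAP.

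Most of this stands. A reader might infer that the trial's type I error simply is 23%. The documents do not support that: the figure holds only if the observed margin is inserted as a constant. Nor should the absence of a named test in a condensed article count as a fault.

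A reader might also blame the margin's wording for the zero-control case. That problem comes from the low incidence. With no control positives a standard ratio method gives an undefined RR or an infinite upper limit, and restating the margin as a ratio does not remove it.

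What the reply does not answer is the power. The relative-risk reading protects the type I error only by using a test to which the stated sample-size arithmetic does not apply.

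**Conclusion.** The point holds in conditional form. The article ties the threshold to an observed incidence, and its sample-size figures match a calculation in which the margin carries no error. If the analysis follows that calculation, type I error at a true five-fold risk is about 23% (17–25%) against a stated 5%. If the margin is a fixed RR of 5 tested with both arms' error, type I error is about 2–7%, but power at RR = 1 is 13–39% at 100 per 100,000 and 46–65% at 300 per 100,000. On neither reading do the stated 5% and 80% hold together over the planned incidence range.

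The reproduction rests on two assumptions the text does not state, one-sided 5% and division by 0.38. The 23% depends little on the second, since its large-sample value does not involve the incidence. The power and zero-control figures do depend on it: division by 0.62 means fewer expected events and makes both less favourable for the tests above.

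**What to change.** State the margin as a ratio fixed in advance: H0: RR ≥ 5 against H1: RR < 5. Decide by the upper one-sided 95% limit of the RR, from a method that includes the sampling error of both arms and is adapted to the reservation-group clusters. Mid-P and score are candidates; mid-P stayed below 5% in the enumeration, whereas score ran slightly above it. Restate the power for that test at 2,000 per arm over the planned incidence range. Say whether alpha is one-sided and whether 38% is the detected or the missed share.

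Also state that with zero control positives the ratio result is inconclusive, and that the absolute risk difference with its confidence interval is then reported.

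The cost is wording in the protocol and SAP. The downside is that the restated power will be below 80%, and at 100 per 100,000 far below it.
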